##### Illness cognitions

Illness cognitions are measured by the Illness Cognition Questionnaire (ICQ) [54]. Illness cognitions reflect ways of reevaluating the aversive character of a chronic disease. The 18-item ICQ includes three generic illness cognitions: helplessness (emphasizing the aversive meaning of the disease), acceptance (diminishing the aversive meaning by learning how to cope with the disease), and perceived benefits (adding positive meaning to the disease, e.g., personal growth). Higher scores reflect higher levels of the illness cognitions.

##### Optimism

The Life Orientation Test – Revised (LOT-R) [55] is used to assess optimism. The LOT-R includes 10 items. Higher scores indicate more optimism.

##### Extraversion and neuroticism

The subscales extraversion and neuroticism of the Dutch version [57] of the Eysenck Personality Questionnaire – Revised Short Scale (EPQ-RSS) [56] will be used to measure both personality traits. Both subscales include 12 items, with higher scores indicating more extraversion and neuroticism.

##### Therapeutic relationship

The Internet-specific Therapeutic Relationship Questionnaire (ITRQ) [58] measures the Internet-specific aspects of the therapeutic relationship during Internet-based interventions. The ITRQ includes two subscales: Internet-specific time and attention (i.e., time lag aspects in communication and the sufficiency of the therapist’s attention), and Internet-specific reflection and comfort (i.e., sharing information with the therapist and the treatment environment being a patient’s home). The ITRQ includes 8 items, with higher scores indicating a better therapeutic relationship. In contrast to the other measures, the ITRQ will be completed only by patients allocated to the intervention condition. Assessment will take place at post-treatment.

#### Cost-effectiveness

##### Health-related quality of life for economic evaluations

The Five-level EQ-5D (EQ-5D-5L) [59] measures HRQOL on five dimensions of health: mobility, self-care, usual activities, pain/discomfort, and anxiety/depression. Scores of this 5-item questionnaire can be translated into quality-adjusted life years (QALYs) for health technology assessments and economic evaluations [60].

##### Productivity losses and medical costs

Two questionnaires of the Institute for Medical Technology Assessment (iMTA) will be used for the measurement of costs in economic evaluations: the iMTA Productivity Cost Questionnaire (iPCQ) [61] and the iMTA Medical Consumption Questionnaire (iMCQ) [62]. The iPCQ assesses productivity losses and includes 12 items which will be presented based on the patient’s answers. The iMCQ is a generic instrument for measuring medical costs. The iMCQ includes questions on the type and frequency of treatment, contact with health care providers, hospitalization, and medication use. The iMCQ includes 31 items—items will be presented based on the answers on the previous items.

##### Capability wellbeing

The ICEpop CAPability measure for Adults (ICECAP-A) [63] is a measure for capability wellbeing for the general adult population for use in economic evaluations. It includes 5 items on stability, attachment, autonomy, achievement, and enjoyment.

### Participant timeline {13}

See Fig. 1 for the SPIRIT figure with the participant timeline.

### Sample size {14}

The power calculation is based on the difference in change of distress from baseline to follow-up between the intervention and the control group. The effect size was based on previous RCTs on (Internet-based) CBT treatment in dialysis patients with a focus on distress-related outcomes (e.g., depression) indicating medium effects [73, 74]. In the absence of studies focusing on a broader spectrum of adjustment problems such as the current study, we used these studies for an estimation of the effect size despite the fact that they focused solely on distress. When using an alpha level of .05 and an effect size of 0.50 (Cohen’s *d* moderate effect), and taking account of potential dropouts, effects for 2 groups of 65 patients yield a power of at least .80.

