**Methods:**

After a screening procedure on adjustment problems, 130 eligible dialysis patients will be randomized to care as usual or the E-HELD intervention. Patients will complete questionnaires on distress (primary outcome measure), several domains of functioning (e.g., physical, psychological, social), potential predictors and mediators of treatment success, and the cost-effectiveness of the intervention, at baseline, 6-month follow-up, and 12-month follow-up. In addition, to take account of the personalized character of the intervention, the Personalized Priority and Progress Questionnaire (PPPQ) will be administered which is a personalized instrument to identify, prioritize, and monitor individual problems over time.

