There are several limitations to consider. As found in previous studies on ICBT in dialysis patients, challenges with computer literacy are likely to occur. This could result in lower inclusion rates due to patients not having access to a computer or Internet. In addition, when patients are enrolled in the study, poor computer skills could lead to drop-out when participating in the study appears to be too difficult. To minimize the risk of drop-out, the therapists who guide the intervention will be highly attentive of these difficulties and will make adjustments if the intervention appears to be too difficult. For example, therapists could choose to communicate via telephone instead of online text messages. Another risk for drop-out is patients’ high disease burden. This risk could be minimized in the same way: regularly monitoring whether ICBT treatment matches the patient’s abilities and making adjustments if necessary (e.g., lowering the intensity).

In conclusion, the present study design will provide insight in the effectiveness of a patient-priorities tailored ICBT intervention in patients with kidney failure who are treated with dialysis. When tailored ICBT proves to be a valuable and effective intervention, the screening procedure and the subsequent ICBT intervention could be implemented in routine care to detect, support, and treat patients struggling with adjustment problems.

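### The stated power of at least .80 after dropouts cannot be reproduced: on the usual two-sided reading, 65 per arm is essentially the number needed with no dropout

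*Protocol article*

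**What the plan says.** The Sample size section of the protocol article defines the quantity that is powered: "The power calculation is based on the difference in change of distress from baseline to follow-up between the intervention and the control group". It gives the inputs, "When using an alpha level of .05 and an effect size of 0.50", and concludes that, "taking account of potential dropouts, effects for 2 groups of 65 patients yield a power of at least .80".

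The Methods part of the abstract fixes what 65 per group means: "130 eligible dialysis patients will be randomized to care as usual or the E-HELD intervention". With 1:1 allocation (Trial design), 65 per arm is the number randomised and not the number expected to complete.

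The Discussion expects some attrition. Its limitations paragraph says that "poor computer skills could lead to drop-out when participating in the study appears to be too difficult", and it also names high disease burden as a dropout risk. No rate is given anywhere in the article.

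The Statistical methods section assigns the primary outcome to a linear mixed model with the baseline score as a covariate. The Data collection section makes the 6-month assessment the primary one.

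**The concern.** An allowance for dropout means that the number randomised exceeds the number that must be analysed. An effect size of 0.50 at two-sided .05 with 80% power is a standard case, and its requirement is very close to 65 per arm. The stated sample size therefore looks like the complete-follow-up requirement with a dropout allowance claimed but not added.

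This is the only power statement in the article, and the Discussion criticises earlier work in this population as underpowered. If the trial ends without a significant difference, readers will take the result as coming from a study that kept at least 80% power after attrition. The stated inputs do not support that on the ordinary reading.

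**Working it through.** **Inputs from the article.** Alpha .05; standardised effect d = 0.50 on change in distress; 1:1 allocation; 65 randomised per arm; target power at least .80.

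**Inputs not in the article, assumed here.** A two-sided test (convention); dropout from 0% to 30%; for the adjusted analysis, a correlation r between baseline and follow-up of 0.3 to 0.7. Dropout is treated as complete loss of the patient.

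**Step 1. Number required with no dropout.** Normal approximation:

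n per arm = 2 × (1.960 + 0.842)² / d² = 2 × 7.85 / 0.25 = 62.8, so 63.

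The t-test version (noncentral t) gives 63.8, so 64. Randomising 65 leaves 1 spare patient per arm, 1/65 = 1.5%.

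**Step 2. Reproducing the stated figure.** With all 65 per arm analysed, power is .808 (t-test) or .813 (normal approximation). The claim of at least .80 is met, but with complete follow-up.

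**Step 3. Power with dropout.** Analysed n per arm = 65 × (1 − dropout); two-sided t-test, d = 0.50.

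| Dropout | Analysed per arm | Power |
|---|---|---|
| 0% | 65 | .808 |
| 1.5% | 64 | .802 |
| 2% | 63.7 | .7996 |
| 5% | 61.75 | .787 |
| 10% | 58.5 | .765 |
| 20% | 52 | .714 |
| 30% | 45.5 | .655 |

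Power crosses .80 at about 2% dropout. The shortfall is small at 5% and clear from 10%.

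**Step 4. Could a one-sided test explain the figure?** At one-sided .05 the requirement is 50.2, so 51 per arm. Then 51/0.80 = 63.75, so 64 randomised per arm would cover 20% dropout, and power with 52 analysed per arm is .813. The figure would then reproduce, but the article declares no one-sided test.

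**Step 5. Could the planned baseline adjustment explain it?** Consider a single follow-up with outcome variance σ² at both times. The variance of change is 2σ²(1 − r), and the residual variance after baseline adjustment is σ²(1 − r²). Their ratio is (1 + r)/2. The effective effect size is therefore:

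- if d is on the SD of change: 0.50 / √((1 + r)/2)
- if d is on the SD of the outcome: 0.50 / √(1 − r²)

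Two-sided t-test power at 20% dropout (52 analysed per arm):

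| r | d on change SD: effective d, power | d on outcome SD: effective d, power |
|---|---|---|
| 0.3 | 0.620, .879 | 0.524, .754 |
| 0.5 | 0.577, .830 | 0.577, .830 |
| 0.6 | 0.559, .806 | 0.625, .884 |
| 0.7 | 0.542, .782 | 0.700, .943 |

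Adjustment restores .80 for some combinations and not for others, and the direction of the dependence on r reverses with the scale of d.

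**The case against.** The strongest reply is that the unadjusted t-test is not the primary analysis. The mixed model adjusts for baseline, and with d on the SD of change it keeps at least .80 at 20% dropout for r from 0.3 to 0.6. At 10% dropout it does so at every r from 0.3 to 0.7 (.829 at r = 0.7). The model also uses all available data, so a patient who misses one assessment may still contribute, and the .714 and .655 figures describe complete loss. This stands. A reader might infer that any dropout takes the trial below 80% power, or that the trial is underpowered. The article supports neither inference: one patient per arm can be lost with power still .80 even unadjusted, and the planned analysis may do better.

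The reply does not rescue the sentence itself. The Sample size section powers a difference in change, gives no correlation and claims no gain from adjustment. Whether the gain suffices depends on two quantities that it does not state.

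A second reply is that sidedness is unstated and a one-sided .05 test would absorb about 20% dropout. The arithmetic is right, but a one-sided primary test in a superiority trial would have to be declared, and none is.

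A third reply is that an article condenses the full protocol, so the dropout rate and similar details may be stated there. Their absence alone is therefore not the point. The point is a positive claim about power after dropout that the inputs printed beside it do not deliver on the standard reading.

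**Conclusion.** The point holds as a fault in the stated justification. On a two-sided .05 two-sample comparison with d = 0.50 on change, 64 analysed per arm are needed, so 65 randomised per arm carries an allowance of about 1.5%. Power is about 81% with complete follow-up, under 80% once dropout exceeds about 2%, about 76% at 10% and about 71% at 20%.

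This rests on the two-sided convention, on assumed dropout rates, and on counting a dropout as fully lost. It says nothing firm about the power of the planned baseline-adjusted model, which at 20% dropout runs from about 75% to 94% over the correlations and scales tried. The statement should be fixed, but no estimand, analysis or enrolment target has to change.

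**What to change.** Restate the power in the Sample size section in one of two ways, without enrolling more patients.

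1. For the unadjusted two-sided comparison: 130 randomised gives about 81% power for d = 0.50 with complete follow-up, and about 71% if 20% drop out.
2. For the planned baseline-adjusted analysis: recalculate and state the sidedness, assumed dropout rate, evaluable number per arm, baseline-to-6-month correlation, and whether d is on the SD of change or of the outcome. For example, at 20% dropout with d on the SD of change, power is about 83% at r = 0.5 and about 78% at r = 0.7.

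The assumed dropout rate and correlation should carry a stated source or be shown as a range.

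The cost is one paragraph. The stated power either becomes less favourable or comes to depend openly on a named correlation.

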### Recruitment {15}

Patient recruitment will take place in several centers in the Netherlands: Radboud university medical center, Nijmegen; Leiden University Medical Center, Leiden; VieCuri Medical Centre, Venlo; Bernhoven Hospital, Uden; Dialysis Center Groningen, Groningen; and Ravenstein Dialysis Centre, Ravenstein. Patients will be recruited from February 2019 until November 2021. Depending on the rate of inclusion, we will contact other centers as well. After screening on the inclusion and exclusion criteria, nephrologists or (research) nurses recruit eligible patients during consultation or dialysis treatment. After 3–6 months, screening will be repeated to include newly started dialysis patients.

## Assignment of interventions: allocation

### Sequence generation {16a}

Eligible patients (i.e., signs of adjustment problems as indicated by the screening questionnaires) will be randomized to the intervention or control group on a 1:1 allocation ratio using computer-generated random numbers. To reduce predictability of a random sequence, a blocking procedure will be used including random block sizes of 4 and 6. In addition, randomization will be stratified by sex, dialysis type, and study site.

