## Methods: participants, interventions and outcomes

### Study setting {9}

The study will be conducted in two academic hospitals (Radboud university medical center, Nijmegen; Leiden University Medical Center, Leiden), two non-academic hospitals (VieCuri Medical Centre, Venlo; Bernhoven Hospital, Uden), and two dialysis centers (Dialysis Center Groningen, Groningen; Ravenstein Dialysis Centre, Ravenstein). All study sites are located in the Netherlands.

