### Intervention description {11a}

#### Procedure E-HELD intervention

Participants allocated to the intervention condition will receive tailored ICBT. The ICBT intervention is guided by a trained psychologist, referred to as the “e-Coach.” All e-Coaches participating in this study have a master’s degree in health or clinical psychology and are supervised by a senior clinical psychologist with post-academic training in CBT. Treatment starts with a face-to-face intake meeting with the e-Coach. When a face-to-face meeting is not possible, the e-Coach will schedule a digital, videoconferencing meeting instead. During the intake, the patient will receive feedback on the screening results using the Personal Profile Chart in which the results are visualized. Based on the discussion of patient’s results, the patient and the e-Coach will determine patient’s top priorities for improvement and formulate treatment goals. Subsequently, the e-Coach will tailor the intervention so that it meets the patient’s needs. In addition, the e-Coach will explain the online environment and explores the patient’s wishes with regard to the intensity and the form of the treatment (e.g., the amount of exercises, a wish for additional phone calls, or a preference for reading texts or practical exercises). Subsequently, the patient will work on the homework assignments for 3 to 4 months.

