## Statistical methods

### Statistical methods for primary and secondary outcomes {20a}

Descriptive statistics (means, standard deviations, medians, and interquartile ranges) of relevant variables will be calculated. In case of non-normally distributed variables, transformations will be applied to allow parametric statistics. Baseline data of the intervention and control condition will be compared to assess similarity. Additionally, several *t*-tests will be performed on the 6-month follow-up data, both on the primary and secondary outcomes.

To examine differences in the primary outcome measure change in distress between patients in the intervention and control condition, a linear mixed-model analysis of variance will be conducted. Linear mixed-effects modeling has superior qualities with regard to missing values and makes use of all available data, making this a full-intention-to-treat analysis. Models will be fitted with full information maximum likelihood estimation. Between-group effects at post-treatment and follow-up will be analyzed with baseline scores of dependent variables as covariates. Time will be operationalized as a continuous variable, because post-treatment assessment will vary across participants as a result of different intervention length. Fixed linear effects of time and condition will be included and random effects of intercept.

Similar mixed-model analyses of variance will be conducted to examine differences in change in the scores on the secondary outcome measurements between the two conditions. In addition, correlational and regression analyses will be performed to assess the potential role of demographic and clinical characteristics and psychological parameters (e.g., treatment expectancies, therapeutic relationship) on the effects of the ICBT intervention.

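### The three stratification factors (sex, dialysis type, study site) are absent from the stated treatment comparisons, so the test is mildly conservative if they predict distress beyond baseline

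*Protocol article*

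**What the plan says.** Under Sequence generation {16a}, allocation is 1:1, "randomization will be stratified by sex, dialysis type, and study site", and "a blocking procedure will be used including random block sizes of 4 and 6". Study setting {9} names six sites.

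Statistical methods for primary and secondary outcomes {20a} sets out the model for distress. On covariates it says: "Between-group effects at post-treatment and follow-up will be analyzed with baseline scores of dependent variables as covariates". On the remaining terms: "Fixed linear effects of time and condition will be included and random effects of intercept". Secondary outcomes receive similar models. The same section adds t-tests that "will be performed on the 6-month follow-up data, both on the primary and secondary outcomes".

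Demographic and clinical characteristics appear in {20a} only in separate correlational and regression analyses of what influences the intervention's effect. They are not named as covariates in the comparison of the arms.

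**The concern.** Stratified blocking makes the arms more alike on the stratification factors than simple randomisation would. This reduces the true sampling variance of the treatment difference when those factors predict the outcome. A model that omits them still counts the variance they explain as residual noise, so its reported standard error exceeds the true one.

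At stake is precision. Confidence intervals are a little too wide, the test rejects less often than its nominal level, and some of the benefit of stratifying is lost. The stated power has little margin at the planned size (first step of the working), so precision that can be recovered by wording alone is worth having.

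**Working it through.** **Inputs from the protocol article.** 65 per arm, d = 0.50, alpha .05 and power of at least .80 (Sample size {14}; two-sided testing is assumed, since sidedness is not stated). Three stratification factors and blocks of 4 and 6 ({16a}). Six sites ({9}).

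**Assumption.** R² is the share of outcome variance explained by the three factors *after* the baseline score. The documents give no value. The range shown is 0, 0.05 and 0.10.

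**1. The plan's own figure.** In standard-deviation units, SE = √(2/65) = 0.1754, and 0.50/0.1754 = 2.850. Power = Φ(2.850 − 1.96) = 0.813 (0.808 by the exact t-test). The stated figure reproduces with all 65 per arm analysed.

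**2. Strata.** 6 sites × 2 sexes × 2 dialysis types = 24 cells, and 130/24 ≈ 5.4 patients per cell. With blocks of 4 and 6, many blocks will end incomplete, so balance within cells is imperfect.

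**3. Upper limit under perfect balance.**
- Reported SE / true SE = 1/√(1 − R²)
- Type I error = 2[1 − Φ(1.96/√(1 − R²))]
- Power without the factors = Φ((2.850 − 1.96)/√(1 − R²))
- Power with the factors = Φ(2.850/√(1 − R²) − 1.96)

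| R² | SE ratio | Type I error | Power without | Power with | Gain |
|---|---|---|---|---|---|
| 0.05 | 1.026 | 0.044 | 0.820 | 0.833 | 1.3 points |
| 0.10 | 1.054 | 0.039 | 0.826 | 0.852 | 2.6 points |

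Power without the factors must be computed from the true, smaller SE. Using the inflated SE as if it were the true one would overstate the gain.

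**4. Simulation of the actual design.** N = 130, permuted blocks of 4 and 6 within the 24 cells, 6,000 runs per setting. It uses one outcome of unit variance, standing for the score after baseline adjustment. Assumed: site shares of 10–25%, 40% in one sex category, 15% in one dialysis type, and R² split equally over the three factors. SE figures are from the null runs.

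| R² | Reported SE, factors omitted | True SD of estimate | Excess | Type I without / with | Power without / with |
|---|---|---|---|---|---|
| 0 | 0.1753 | 0.1767 | none | 0.051 / 0.052 | 0.807 / 0.802 |
| 0.05 | 0.1752 | 0.1718 | 2.0% | 0.046 / 0.049 | 0.818 / 0.822 |
| 0.10 | 0.1751 | 0.1690 | 3.6% | 0.044 / 0.053 | 0.809 / 0.840 |

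Monte Carlo standard errors are √(0.05 × 0.95/6000) = 0.003 for type I error and √(0.81 × 0.19/6000) = 0.005 for power. A repeat simulation at R² = 0.10 gave an SE about 3–5% too large, type I error of about 0.041, and power of about 0.82 without and 0.85 with the factors.

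**5. Reading.** The simulation is milder than the perfect-balance limit, as incomplete blocks would lead one to expect, and agrees with it in direction.

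**The case against.** **The article may simply be condensed.** It does not call its list of terms exhaustive, and a full covariate list is often left to the analysis plan. This stands in part: if the unseen plan includes the factors, only the article's description needs correcting. But {20a} gives the fixed effects, random effect, covariate, estimator and coding of time. A specification that detailed, naming none of the three design factors, is a stated model and does not match {16a}. The grouping level of the random intercept is not named; for repeated measures the patient is the natural reading, so it does not supply a site term.

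**The effect may be nil.** This stands. Only variance explained beyond baseline distress counts, and the documents do not show that sex, dialysis type or site explains any.

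**Stronger readings that the documents do not support.** A reader might infer that the trial risks a biased or falsely positive result. It does not from this cause: the error is conservative and the estimate is unbiased.

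A reader might also fold in the therapist. The article says "The ICBT intervention is guided by a trained psychologist", controls have no e-Coach, and the model has no e-Coach term. Shared therapists would push the standard error the other way. With 4 e-Coaches and R² = 0.10, simulated type I error of the model without the factors is 0.049, 0.063 and 0.092 at assumed intraclass correlations of 0.01, 0.02 and 0.05; with 8 e-Coaches and 0.05 it is 0.066. But the e-Coach is not a randomisation factor, and neither the number of e-Coaches nor the correlation is stated. It is a separate issue. It also means that adding the strata cannot be promised to give exactly correct standard errors: with 4 e-Coaches and a correlation of 0.05, type I error is 0.092 without the factors and 0.102 with them.

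**Conclusion.** The stated analysis does not carry the stratification used at randomisation. The consequence is a modest loss of precision. With an assumed 5–10% of post-baseline variance explained by the strata, the standard error is about 2–5% too wide, type I error is about 0.041–0.046, and about 0–3 points of power are forgone at 65 per arm. At R² = 0 there is no mismatch, and adjustment costs about half a point of power (0.807 to 0.802), which is within simulation error. The direction is well founded; the size rests on an R² that the documents do not give. The point is worth correcting because the remedy is nearly free, but it does not threaten the validity of a positive finding.

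**What to change.** In {20a}, and in the analysis plan if it is silent, add sex, dialysis type and study site as main effects to the primary and secondary mixed models. This takes 1 + 1 + 5 = 7 degrees of freedom out of 130 patients. Do not fit the full 24-cell cross, which is too sparse. If small centres join, as Recruitment {15} allows, pool them or use a random site intercept.

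State that between-group inference rests on these models and that the 6-month t-tests, which use neither baseline nor strata, are descriptive.

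Optionally, and as a separate matter, add a sensitivity analysis with a random e-Coach effect in the intervention arm only. Its variance will be poorly estimated if there are few e-Coaches.

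The cost is wording. No new data are needed, because the factors must be known at randomisation, and trial conduct does not change.
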